### Outcome measures and schedule

2.8

#### Evaluation of the primary outcome

2.8.1

The primary outcome of the clinical trial is the changes in SCORAD total scores and sub-scores at week 4 as compared to that at the baseline.

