**Methods/design::**

This study is a single-center, randomized, double-blind, placebo-controlled, and investigator-initiated clinical trial. A total of 60 patients between 7 and 65 years of age with AD and respiratory disorders who received a diagnosis of AD by Hanifin and Rajka criteria who scored 15 to 50 in a scoring atopic dermatitis (SCORAD) will be enrolled. Participants will be randomly assigned to the SCRT or placebo group in a ratio of 1:1 and they will have a visit schedule comprising 4 visits including a screening visit during 8 to 10 weeks. The participants will be administered SCRT or placebo 3 times a day for 4 weeks. The primary outcome will be measured by a change of the SCORAD index. The secondary outcomes will be measured by changes in the dose and frequency of usage of the AD ointment, dermatology life quality index scores, pruritus and sleep disorder in visual analog scale, skin moisture content, skin surface temperature, Hamilton anxiety rating scale scores, depression rating scale scores, stress/autonomic nervous function test, and attention deficit hyperactivity disorder survey scores at week 4 as compared to those at the baseline.

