### Sample size calculation

2.7

The primary objective of this investigator-initiated clinical trial is to demonstrate a larger reduction in the AD symptom in the experimental group than the placebo group after 4 weeks of treatment and to validate the efficacy of SCRT in AD-related respiratory symptoms. To calculate the sample size, we anticipated that the mean changes in SCORAD scores after 4 weeks was 13.8 (*μt*) in the SCRT group and 7.9 (*μc*) in the placebo group. The standard deviation (*σ*) between the SCRT and placebo groups was assumed to be 8.2. The type 2 error at a 5% significance level was set as 0.2 and the power of the test was maintained at 80%. Taking a 20% dropout rate into account and maintaining the 1:1 allocation ratio between the SCRT and placebo groups, the final sample size was 30 in each group.

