### Statistical analyses

2.9

Appropriate statistical tests will be performed according to the characteristic of the data, the number of associated variables and their correlations, and the state of distribution. Windows Strategic applications software will be used for analysis. At a significance level of 5% and power of 80%, 95% confidence interval will be reported for the differences in the results between the groups. Participants with results of at least 1 efficacy outcome after administration of the investigational drug after randomization will be included for efficacy assessment. In addition, all subjects who will receive the investigational drug at least once and visit the hospital will be included for the safety assessment. Chi-square test or Fisher exact test will be used for the discrete variables, and analysis of variance or Kruskal–Wallis test will be used for the continuous variables.

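### The primary outcome joins the SCORAD total and its sub-scores without saying which one decides success, while the abstract and the sample size rest on one SCORAD score

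*Protocol article*

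**What the plan says.** Three places in the protocol article describe what the trial is to be judged on.

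- Section 2.8.1 (Evaluation of the primary outcome): "The primary outcome of the clinical trial is the changes in SCORAD total scores and sub-scores at week 4", compared with baseline. The number of sub-scores is not given.
- Abstract, Methods/design: "The primary outcome will be measured by a change of the SCORAD index". Sub-scores are not mentioned.
- Section 2.7 (Sample size calculation): "we anticipated that the mean changes in SCORAD scores after 4 weeks was 13.8" in the SCRT group and "7.9 (*μc*) in the placebo group", with a standard deviation that "between the SCRT and placebo groups was assumed to be 8.2". This is one SCORAD comparison; no effect is assumed for any sub-score. On error rates: "The type 2 error at a 5% significance level was set as 0.2 and the power of the test was maintained at 80" percent.

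On testing, section 2.9 (Statistical analyses) gives one general level: "At a significance level of 5% and power of 80%, 95% confidence interval will be reported" for the between-group differences. Section 2.10 (Efficacy assessment) applies an independent t test to the assessment items. Neither section ranks the total above the sub-scores, states a success rule or divides the 5%. Section 2.9 also says that the choice of test will depend on the number of variables and their correlations, but that is not a multiplicity rule.

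**The concern.** Section 2.8.1 describes a primary outcome with several components, whereas the abstract and section 2.7 describe a trial with one. With several components, the text has to say what counts as success, and it does not. If the total were null and one sub-score significant, the trial could be reported as positive on its primary outcome without departing from section 2.8.1. The chance of a false efficacy claim then depends on a choice that could be made after the results are known.

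**Working it through.** **Inputs from the article.** Mean changes 13.8 and 7.9 (difference 5.9), SD 8.2, 5% level, 80% power, 20% dropout, 30 per group (section 2.7). Completers per group: 30 × 0.8 = 24.

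**Inputs assumed.** The number of sub-scores (three, with two and six as alternatives), equal contributions of the sub-scores to the total, and the correlation between sub-scores (0 to 0.9). The article gives none of these. It does not state one- or two-sided testing either, so both are considered.

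**Step 1: reproduce the planned size.** n per group = 2 (z_α + z_β)² SD² / difference².
- One-sided 5%: 2 × (1.645 + 0.842)² × 8.2² / 5.9² = 23.9, so 24; 24 / 0.8 = 30. This matches the article.
- Two-sided 5%: 2 × (1.960 + 0.842)² × 8.2² / 5.9² = 30.3, so 31; 31 / 0.8 = 38.75, so 39. This does not match.

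The stated 30 is therefore what a single comparison at an undivided one-sided 5% gives. Sidedness is a separate matter. What counts here is that no part of the 5% was set aside for further primary tests.

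**Step 2: upper reference if any one score suffices.** For k independent tests at 5%, the chance of at least one false positive is 1 − 0.95^k: 9.8% for k = 2, 14.3% for k = 3, 18.5% for k = 4 and 30.2% for k = 7. The total is built from the sub-scores, so the tests are correlated and the true figure is lower.

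**Step 3: allow for the correlation.** Simulation under no treatment effect, 24 per group, with a two-sample t test on each sub-score and on their sum, each at 5%. The table gives the chance that at least one is significant with three sub-scores.

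| Sub-score correlation | Two-sided | One-sided |
|---|---|---|
| 0 | about 16% | about 16% |
| 0.5 | about 13% | about 12% |
| 0.7 | about 11% | about 10% |
| 0.9 | about 9% | about 8% |

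Two-sided, over the same correlations, the range is about 7% to 12% with two sub-scores and about 11% to 28% with six. With three sub-scores, unequal weights (1, 2, 1.5) in place of equal ones change the result by about 0.1 percentage point or less.

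**Step 4: the other two readings.**
- The total alone decides: the error is 5%.
- All four scores must be significant: the error is below 3% at every correlation run.

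**Step 5: could the planned size carry an adjustment?** Bonferroni over four tests uses 0.05 / 4 = 0.0125 each. With the total-score effect of 5.9 and SD 8.2:
- One-sided: 2 × (2.241 + 0.842)² × 8.2² / 5.9² = 36.7, so 37; 37 / 0.8 = 46.25, so 47 per group. Power with 24 completers is about 60%.
- Two-sided: 2 × (2.498 + 0.842)² × 8.2² / 5.9² = 43.1, so 44; 44 / 0.8 = 55 per group. Power with 24 completers is about 50%.

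The planned 30 per group leaves no room for a Bonferroni split at 80% power.

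**The case against.** The strongest reply is that the article points to a single intended endpoint. The abstract names one index, section 2.7 sizes the trial on one difference, and section 2.8.1 uses the singular for one instrument at one time point. If the total leads and the sub-scores support it, the error is 5%. Multiplicity procedures also often sit in an analysis plan, and none is shown here.

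Much of this stands. A reader might infer that the trial will test every sub-score at 5% as a route to success, and hence that its efficacy claim has no 5% control. The article does not support that reading. It gives one general significance level, never assigns 5% score by score, and states no any-one rule. Inflation follows under one of three open readings; under the other two the error is 5% or less. The absence of an adjustment method is not in itself a defect in a condensed article.

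The definition is not rescued, however. Saying what the primary outcome is belongs to the protocol, and section 2.8.1 says it in a way that differs from the abstract and section 2.7. The evidence of intent is indirect and does not override the explicit wording. A later analysis plan could not cleanly repair that mismatch, and a Bonferroni adjustment would not fit the planned size.

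**Conclusion.** The concern holds as an ambiguity in the definition of the primary outcome. Section 2.8.1 places the total and the sub-scores together at the primary level without a success rule, in conflict with the abstract and with the basis of the sample size. The wording allows a positive claim on a sub-score when the total is null.

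If that route were used at the general 5% level, the false-positive rate would be about 9% to 16% two-sided with three sub-scores, and slightly lower one-sided. With two to six sub-scores the range is about 7% to 28%. The size rests on the assumed number of sub-scores, their equal contributions, their correlation and 24 completers per group. The direction does not depend on these choices: the rate exceeded 5% in every any-one case run.

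**What to change.** In section 2.8.1, write: *The single primary outcome is the change in SCORAD total score from baseline to week 4.* Move the sub-scores to section 2.8.2 as secondary outcomes, and add that they cannot by themselves support the efficacy claim.

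This brings section 2.8.1 into line with the abstract and section 2.7, needs no new data and leaves the planned 30 per group unchanged. The only cost is giving up the option to claim success on a sub-score. The change should be made before the allocation is unblinded.

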#### Evaluation of the secondary outcomes

2.8.2

The secondary outcomes of the clinical trial are the changes in the dose and frequency of usage of the AD ointment, dermatology life quality index scores, pruritus and sleep disorder in visual analog scale, skin moisture content, skin surface temperature, Hamilton anxiety rating scale scores, depression rating scale scores, stress/autonomic nervous function test, and attention deficit hyperactivity disorder survey scores at week 4 as compared to those at the baseline.

### Statistical analyses

2.9

Appropriate statistical tests will be performed according to the characteristic of the data, the number of associated variables and their correlations, and the state of distribution. Windows Strategic applications software will be used for analysis. At a significance level of 5% and power of 80%, 95% confidence interval will be reported for the differences in the results between the groups. Participants with results of at least 1 efficacy outcome after administration of the investigational drug after randomization will be included for efficacy assessment. In addition, all subjects who will receive the investigational drug at least once and visit the hospital will be included for the safety assessment. Chi-square test or Fisher exact test will be used for the discrete variables, and analysis of variance or Kruskal–Wallis test will be used for the continuous variables.

### Efficacy assessment

2.10

Changes in the assessment items at week 4 as compared to the baseline in each group will be presented, and the differences between the experimental and control groups will be analyzed using the independent *t* test. Additionally, changes in the assessment items at week 4 as compared to before drug administration in each group will be analyzed using the paired *t* test. The baseline variables for each efficacy outcomes and non-homogenous demographic variables will be adjusted according to the covariates and will be used for analysis of covariance.

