### Study phase

2.3

During screening at the hospital, the eligibility of the participants will be adjudicated based on their medical history, medication history, results of blood and urine tests, vital signs, SCORAD index, and Hanifin and Rajka diagnostic criteria. Then the participants determined to be eligible for the trial will visit the hospital (visit 1) within 2 weeks after screening and will be randomly assigned to the treatment or the control group. After group allocation, various surveys including AD survey and physical examination will be conducted, and the participants will be administered with the investigational drug 3 times a day for 4 weeks. After 4 weeks, the participants will be asked to visit the hospital again (visit 2) and undertake the same surveys, examinations, and blood investigations as those at visit 1. For the next 4 weeks, all drugs will be withdrawn except Lacticare, a concomitant drug, and the participants will be asked to visit the hospital (visit 3) and undertake the same surveys and investigations. The specific schedules and types of examinations are summarized in Table 1.

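### Section 2.10 gives two between-group analyses of the same week-4 outcome without saying which decides, and picks ANCOVA covariates by observed imbalance

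*Protocol article*

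**What the plan says.** Section 2.10 (Efficacy assessment) first states that "the differences between the experimental and control groups will be analyzed using the independent" *t* test, applied to the week-4 change. A paired t test within each group follows. The section closes with an ANCOVA, for which "The baseline variables for each efficacy outcomes and non-homogenous demographic variables will be adjusted according to the covariates". It does not list the demographic variables, define non-homogeneous, or rank the t test against the ANCOVA.

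Section 2.9 (Statistical analyses) opens with "Appropriate statistical tests will be performed according to the characteristic of the data", and also with regard to the variables' number, correlations and distribution. It ends by assigning ANOVA or Kruskal–Wallis to continuous variables. It also says that a "95% confidence interval will be reported for the differences in the results between the groups", which points to two-sided inference at 5%.

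Section 2.8.1 makes the week-4 change in SCORAD total and sub-scores the primary outcome. Section 2.7 sizes the trial on an unadjusted comparison of mean changes.

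**The concern.** The unadjusted t test on change and the baseline-adjusted ANCOVA estimate the same treatment difference, but they can return different p values on the same data. With neither named as decisive, a reader of the final report cannot tell whether the one put forward was chosen in advance.

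The covariate rule adds a second freedom. In a randomised trial a demographic imbalance between arms is due to chance. Selecting covariates on that basis ignores whether they predict SCORAD. It also requires the data split by group before the model is known. With no threshold and no list of variables, the analyst decides what counts as non-homogeneous.

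Precision matters too. The t test on change is the weaker of the two analyses, and the trial is small.

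**Working it through.** **Inputs.** From section 2.7: "mean changes in SCORAD scores after 4 weeks was 13.8" in the SCRT group and "7.9 (*μc*) in the placebo group", so the difference is 13.8 − 7.9 = 5.9; SD 8.2, taken as the SD of the change; 80% power; 5% level with sidedness not stated; 20% dropout; 30 per group. The baseline to week-4 correlation ρ is not in the document. It is assumed here to lie between 0.3 and 0.7, with equal SDs at the two times.

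**The plan's own figure.** n per group = 2(z₁₋α + z₀.₈)² × (8.2/5.9)², with (8.2/5.9)² = 1.932.
- One-sided 5%: 2 × (1.645 + 0.842)² × 1.932 = 23.9, so 24; 24/0.8 = 30. This reproduces the stated size.
- Two-sided 5%: 2 × (1.960 + 0.842)² × 1.932 = 30.3, so 31; 31/0.8 = 38.75, so 39. This does not.

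The stated 30 per group therefore fits an unadjusted one-sided comparison. After dropout, 30 × 0.8 = 24 per arm are evaluable.

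**Two-sided power at 24 per arm** (noncentral t):
- t test on change: standard error 8.2 × √(2/24) = 2.367; noncentrality 5.9/2.367 = 2.49; 46 df; power 68.4%.
- ANCOVA on baseline: residual SD = 8.2 × √((1+ρ)/2), 45 df.

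| ρ (assumed) | Variance factor (1+ρ)/2 | Residual SD | Noncentrality | Power |
|---|---|---|---|---|
| 0.3 | 0.65 | 6.61 | 3.09 | 85.7% |
| 0.5 | 0.75 | 7.10 | 2.88 | 80.4% |
| 0.7 | 0.85 | 7.56 | 2.70 | 75.3% |

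Power reaches 80% at ρ of about 0.52 or less. At ρ = 0.8 it is 72.9%.

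**Type I error by simulation**, nominal 5%, 24 per arm, normal data, ρ 0.3 to 0.7. Unless noted, there were 10,000 null runs per setting and four demographic covariates, with a covariate added when its between-arm p value was below 0.05.

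| Rule | Type I error |
|---|---|
| t test alone | 5.0–5.3% |
| Kruskal–Wallis alone | 4.8–5.2% |
| ANCOVA, baseline only, fixed | 5.0–5.1% |
| ANCOVA with imbalance-selected covariates | 4.6–4.9% |
| Success if either t test or ANCOVA is significant | 6.9–7.6% |
| Success if any of t test, Kruskal–Wallis or selected-covariate ANCOVA is significant | 7.4–8.5% |
| Normality test, then t test or Kruskal–Wallis (20,000 runs) | 4.6–5.2% |

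A looser selection rule (p below 0.2, stronger covariates) gave 4.1% for the selected ANCOVA. Simulated power (4,000 runs) for fixed against imbalance-selected ANCOVA was 84.0% against 83.3%, 79.9% against 79.4%, and 74.3% against 73.9% at ρ = 0.3, 0.5 and 0.7. Selection therefore costs under one percentage point. These simulated powers lie slightly below the formula values, so the 0.52 threshold is approximate.

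**The case against.** **The article is condensed, and a separate analysis plan may name the decisive model.** That would excuse silence. Section 2.10 is not silent: it states two between-group analyses and a data-dependent covariate rule. The point stands on what is written.

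**The protocol does not say that the smallest p value wins.** Correct. Section 2.9 selects tests by data type and distribution, and a rule of that kind held its level in the simulation. With two arms ANOVA is the t test, and the sentence naming ANOVA and Kruskal–Wallis may refer to baseline or general comparisons. The clear overlap is therefore t test against ANCOVA, and the inflated error rates are an upper range.

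**Baseline adjustment is already planned.** Also correct. The remedy mostly promotes an analysis that section 2.10 already contains.

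**A reader might infer that imbalance-based selection makes the p value invalid.** The simulation does not show this; the error stayed at or below 5%.

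**A reader might infer that the baseline is contaminated**, because section 2.3 says "After group allocation, various surveys including AD survey and physical examination will be conducted". The document does not support this. Section 2.3 lists SCORAD among the screening measures, so a pre-randomisation value exists. It also describes the visit 1 surveys before drug administration, and section 2.6 keeps participants and investigators blinded. A blinded pre-dose value cannot carry a treatment effect.

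**Conclusion.** The point holds in a limited form. Section 2.10 leaves open which of two analyses decides the week-4 comparison, and it fixes the covariates by a rule that can be applied only after the arms have been compared at baseline. In the worst case, where either analysis may be claimed, type I error is about 7% to 8%, and about 8% if Kruskal–Wallis is allowed as well. The covariate rule adds discretion and possibly non-prognostic covariates, but no inflation of its own.

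It would be tempting to say that one ANCOVA restores the planned power. That depends on a correlation the document does not give. At 24 evaluable per arm, two-sided power is about 86% to 75% for ρ from 0.3 to 0.7, assuming equal SDs, against 68% for the t test. The underlying shortfall comes from a sample size that reproduces only with a one-sided 5% test, which is a separate matter.

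Nor does one ANCOVA settle the overall error rate. Section 2.8.1 makes the sub-scores primary alongside the total, and the fix helps there only in so far as it names the total score as primary.

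**What to change.** In section 2.10, name a single primary analysis: ANCOVA of week-4 SCORAD total (or its change; the treatment estimate is the same once baseline is in the model) on treatment, baseline SCORAD and age group (7–14, 15–65, the bands used in section 2.4), tested two-sided at 5% and reported with a 95% confidence interval. State that the independent t test and a rank test are sensitivity analyses. Delete the adjustment for non-homogeneous demographic variables. In section 2.9, limit the general sentence on choosing tests so that it does not override the primary model.

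The cost is wording in sections 2.9 and 2.10 and one or two degrees of freedom. No new data are needed.

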#### Inclusion criteria

2.2.2

The subjects of this study should meet all the following criteria:

(1)Male and female patients between 7 and 65 years of age, scoring 15 to 50 in a scoring atopic dermatitis (SCORAD), and having more than 3 of major criteria and 3 of minor criteria based on the Hanifin and Rajka diagnostic criteria(2)Patients marking more than 1 respiratory disease and symptoms in the questionnaire survey for respiratory disorders(3)Those who fully understand our study after detailed explanation, and voluntarily agree to participate and provide written consent to undertake precautions (in case of a child, both the child and the parent should sign the consent form)

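### The screening SCORAD could serve as a second pre-dose covariate in a fixed primary ANCOVA: a low-cost gain of uncertain size, not an error

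*Protocol article*

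**What the plan says.** The protocol article places SCORAD before dosing as follows.

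- **Screening.** Study phase (2.3) lists the eligibility information, including "results of blood and urine tests, vital signs, SCORAD index, and Hanifin and Rajka diagnostic criteria". Inclusion criteria (2.2.2) require "scoring 15 to 50 in a scoring atopic dermatitis (SCORAD"), so a screening score must exist.
- **Visit 1.** Eligible patients "will visit the hospital (visit 1) within 2 weeks after screening and will be randomly assigned". Then: "After group allocation, various surveys including AD survey and physical examination will be conducted". SCORAD is not named here.
- **Visit 2 (week 4).** Participants "undertake the same surveys, examinations, and blood investigations as those at visit 1".
- **Primary outcome (2.8.1).** The "changes in SCORAD total scores and sub-scores at week 4 as compared to that at the baseline". Baseline is not tied to a visit.
- **Analysis (2.10).** The "differences between the experimental and control groups will be analyzed using the independent" t test. The same section adds covariate adjustment: "The baseline variables for each efficacy outcomes and non-homogenous demographic variables will be adjusted according to the covariates", for use in an analysis of covariance. It does not say which of the two is primary.

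**The concern.** Visit 2 must yield the primary SCORAD and repeats the visit 1 assessments, so SCORAD is very probably scored at visit 1 too. The database would then hold two readings up to 2 weeks apart, both before the first dose. One SCORAD reading is a noisy measure of a fluctuating disease, and a second can sharpen the adjustment. The text of 2.10 gives the screening reading no role, and it leaves open whether any covariate adjustment enters the primary comparison.

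What is at stake is precision, not bias. The trial has little power to spare: its 30 per arm are 24 after the planned 20% dropout.

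**Working it through.** **Inputs.** From Sample size calculation (2.7): mean changes 13.8 and 7.9, so the difference is 5.9; SD 8.2, taken here as the SD of change; 5% significance; 80% power; 20% dropout; 1:1 allocation. From Statistical analyses (2.9): a 95% confidence interval, which implies a two-sided 5% test. The documents give no correlations, so all of those below are assumed.

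**The plan's own figure.** n per arm = 2 × [8.2 × (z for alpha + z for power) / 5.9]².

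- One-sided 5%: 23.88, so 24; 24 / 0.8 = 30. This matches the plan.
- Two-sided 5%: 30.32, so 31; 31 / 0.8 = 38.75, so 39. This does not match.

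The power figures below therefore use 24 evaluable per arm with a two-sided 5% test (noncentral t).

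**Unadjusted t test on change.** SD 8.2, 46 df: power 68.4%.

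**ANCOVA formulas.** Assume equal variance at all three readings. Let ρ1 be the visit 1 to week-4 correlation, ρ2 the screening to week-4 correlation, and r the screening to visit 1 correlation.

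- Variance of one reading: V = 8.2² / [2(1 − ρ1)].
- Residual variance, one baseline: V(1 − ρ1²), 45 df.
- Residual variance, two baselines: V(1 − R²), where R² = (ρ1² + ρ2² − 2ρ1ρ2r) / (1 − r²), 44 df. If ρ1 = ρ2 = ρ, then R² = 2ρ² / (1 + r).

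**Worked case, ρ1 = 0.6.** V = 67.24 / 0.8 = 84.05. One baseline: 84.05 × 0.64 = 53.79, SD 7.33, power 77.8%. Then add screening with r = 0.8:

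- ρ2 = 0.6: R² = 0.72 / 1.8 = 0.40; variance 84.05 × 0.60 = 50.43, SD 7.10, power 80.4%.
- ρ2 = 0.5: R² = (0.36 + 0.25 − 0.48) / 0.36 = 0.361; variance 53.70, SD 7.33, power 77.9%.

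**Range.**

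| ρ1 | ρ2 | r | Variance, two baselines / one | Power, one baseline | Power, two baselines |
|---|---|---|---|---|---|
| 0.5 | 0.4 | 0.8 | 1.00 | 80.4% | 80.4% |
| 0.6 | 0.5 | 0.8 | 1.00 | 77.8% | 77.9% |
| 0.5 | 0.5 | 0.8 | 0.96 | 80.4% | 81.8% |
| 0.6 | 0.6 | 0.8 | 0.94 | 77.8% | 80.4% |
| 0.65 | 0.65 | 0.7 | 0.87 | 76.6% | 82.0% |
| 0.3 | 0.3 | 0.3 | 0.95 | 85.7% | 87.4% |
| 0.5 | 0.5 | 0.5 | 0.89 | 80.4% | 84.7% |
| 0.7 | 0.7 | 0.7 | 0.83 | 75.3% | 82.7% |

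The last three rows set all correlations equal, so the ratio reduces to (1 + 2r) / (1 + r)². Where screening predicts week 4 only through visit 1 (ρ2 = ρ1 × r, as in the first row, 0.5 × 0.8 = 0.4), the gain is nil.

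In the ρ1 = 0.6, r = 0.8 case, replacing the t test by ANCOVA adds 77.8 − 68.4 = 9.4 points and the screening score adds at most 80.4 − 77.8 = 2.6. At 0.7 throughout, the two steps are about equal: 6.9 and 7.4 points.

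**The case against.** The strongest objection is that the plan contains no error here. ANCOVA on one baseline is standard and valid, and a covariate list is often settled in an analysis plan that is not shown. This stands, and it is why the point is offered as an improvement and not as a correction. It does not remove the point. Section 2.10 does describe its analyses and leaves the t test and the ANCOVA unranked, and the suggested wording is specific and costs almost nothing.

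A reader might infer that the plan has decided to adjust for one baseline only and so throws the screening score away. The documents do not support that. Section 2.10 speaks of baseline variables in the plural without saying how many readings are meant, baseline is not tied to a visit, and the screening score is nowhere excluded. One value per outcome is the natural reading, but no more than that. The visit 1 SCORAD is itself inferred, since the schedule table is not shown.

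A reader might also take the equal-correlation rows as the expected gain. They assume that two untreated readings at most 2 weeks apart agree no better than readings 4 weeks apart that span treatment. That is favourable. Selecting patients on a screening score of 15 to 50 restricts its range and may weaken its correlation with later scores, which would reduce the gain further.

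**Conclusion.** The point holds as an optional gain in efficiency. Two pre-dose SCORAD readings very probably exist, and the text gives the screening one no role. Using it in a prespecified model introduces no bias, because it precedes both randomisation and dosing.

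The size is uncertain. When the pre-dose readings agree better with each other than with week 4, the cut in residual variance runs from nil to about 13% in the cases examined. The upper end needs screening to predict week 4 as well as visit 1 does, with pre-dose agreement little higher than that (0.65 with 0.7). Under the more cautious pattern (0.8 between pre-dose readings, 0.5 to 0.6 with week 4) the gain is 0 to about 3 points of power. In that pattern the larger gain comes from making ANCOVA the primary analysis at all. These figures rest on assumed correlations, equal variances, and reading the plan's 8.2 as the SD of change.

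**What to change.** In 2.10, state that the primary comparison is an ANCOVA of the week-4 change in total SCORAD on treatment arm and visit 1 SCORAD, with visit 1 as the reference for change and screening SCORAD as an additional prespecified covariate. In 2.3 or 2.8.1, say outright that SCORAD is scored at visit 1 before the first dose. The t test can stay as a supporting analysis. Fix the wording before unblinding.

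The cost is a line or so of text and one degree of freedom for the extra covariate (45 to 44 at 24 per arm). If the schedule is as inferred, no new visit, measurement or patient is needed.
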